## Abstract

**Background:**

Antibiotic-resistant infections have become a public health crisis that is driven by the inappropriate use of antibiotics. In the USA, antibiotic stewardship programs (ASP) have been established and are required by regulatory agencies to help combat the problem of antibiotic resistance. Post-operative antibiotic use in surgical cases deemed low-risk for infection is an area with significant overuse of antibiotics in children. Consensus among leading public health organizations has led to guidelines eliminating post-operative antibiotics in low-risk surgeries. However, the best strategies to de-implement these inappropriate antibiotics in this setting are unknown.

**Methods/design:**

A 3-year stepped wedge cluster randomized trial will be conducted at nine US Children’s Hospitals to assess the impact of two de-implementation strategies, order set change and facilitation training, on inappropriate post-operative antibiotic prescribing in low risk (i.e., clean and clean-contaminated) surgical cases. The facilitation training will amplify order set changes and will involve a 2-day workshop with antibiotic stewardship teams. This training will be led by an implementation scientist expert ([name]) and a pediatric infectious diseases physician with antibiotic stewardship expertise ([name]). The primary clinical outcome will be the percentage of surgical cases receiving unnecessary post-operative antibiotics. Secondary clinical outcomes will include the rate of surgical site infections and the rate of *Clostridioides difficile* infections, a common negative consequence of antibiotic use. Monthly semi-structured interviews at each hospital will assess the implementation process of the two strategies. The primary implementation outcome is penetration, which will be defined as the number of order sets changed or developed by each hospital during the study. Additional implementation outcomes will include the ASP team members’ assessment of the acceptability, appropriateness, and feasibility of each strategy while they are being implemented.

**Discussion:**

This study will provide important information on the impact of two potential strategies to de-implement unnecessary post-operative antibiotic use in children while assessing important clinical outcomes. As more unnecessary medical practices are identified, de-implementation strategies, including facilitation, need to be rigorously evaluated. Along with this study, other rigorously designed studies evaluating additional strategies are needed to further advance the burgeoning field of de-implementation.

**Trial registration:**

NCT04366440. Registered April 28, 2020, https://clinicaltrials.gov/ct2/show/NCT04366440.

**Supplementary Information:**

The online version contains supplementary material available at 10.1186/s13012-021-01096-1.

Contributions to the literature
This study will evaluate the impact of two strategies, order set review and modification, and order set review and modification plus facilitation, as de-implementation strategies to eliminate unnecessary antibiotic use in children undergoing surgery.This study is one of the first to evaluate the impact of facilitation in de-implementation of unnecessary medical care, which will help inform specific tailored strategies for effective de-implementation in healthcare settings.This study, through its focus on reduction of inappropriate prescribing, will provide further insights into multi-level factors affecting de-implementation including the influence of the strength of the evidence-base, the impact of engaged clinical champions, and the organizational structures most effective.This study will demonstrate the importance of implementation science in advancing the field of antimicrobial stewardship.

## Background

Antibiotics have revolutionized healthcare by treating life-threatening infections and preventing infections for patients requiring needed surgical procedures. Unintended consequences of antibiotic use, worsened by unnecessary use, is the development of antibiotic resistant bacteria and *Clostridioides difficile* infections (CDI) which harm countless numbers of children every year [1–4]. The current rate of antibiotic resistant infections is now considered a major worldwide public health crisis by the World Health Organization [5, 6]. Significant antibiotic overuse occurs among children receiving unnecessary postoperative antibiotic prophylaxis. Although the Centers for Disease Control and Prevention’s (CDC) surgical site infection (SSI) prevention guideline do not recommend postoperative doses for low-risk procedures (clean or clean-contaminated) [7], empirical literature shows overuse occurs in up to 40% of surgical cases [8–10]. Furthermore, these excess doses put children at unnecessary risk. For example, even one additional dose of surgical prophylaxis in a child is associated with a sixfold increased risk for CDI [9]. Further, this overprescribing has not reduced the amount of post-operative complications in clean and clean contaminated surgical cases [11].

Consensus is building among professional organizations regarding the appropriate use of antibiotics to prevent SSIs while also mitigating overuse. In 2017, based on high-quality studies, CDC published SSI prevention guidelines strongly recommending to limit surgical antibiotic prophylaxis to one perioperative dose for clean and clean-contaminated cases [7]. The American Academy of Pediatrics (AAP) Committee on Infectious Diseases published five Choosing Wisely Items, the second of which stated not to “continue prophylaxis after the incision is closed for uncomplicated clean and clean-contaminated procedures” [12].

Antibiotic stewardship programs (ASP) interact with clinicians to help them prescribe antibiotics appropriately to limit the development of antibiotic resistant bacteria, reduce unnecessary adverse drug reactions, and prevent CDI. The CDC recommends that for hospital-based ASPs to be successful they should possess seven core elements [13] (Table 1). A key core element is that ASPs perform actions. These evidence-based actions/strategies include requiring clinicians to obtain approval prior to prescribing an antibiotic, prospectively auditing and providing feedback to clinicians after an antibiotic has been prescribed, and implementing guidelines to ensure the correct antibiotic is given at the correct dose for the correct duration. Frequently, ASPs target eliminating unnecessary durations of antibiotics such as postoperative antibiotics. An emerging body of literature highlights that unnecessary or inappropriate medical practices (e.g., post-operative prophylactic antibiotics) can be very difficult to eliminate [14]; however, evidence is converging to suggest that engagement of stakeholders, such as hospital administrators, departmental leadership, and clinicians, is essential to making meaningful progress toward reducing unnecessary medical practices [15–17].

**Table 1 Tab1:** Core elements for hospital antibiotic stewardship programs

Core element	
Leadership commitment	
Accountability	
Pharmacy expertise	
Action	
Tracking	
Reporting	
Education	

The overall goal of the Optimizing Perioperative Antibiotic in Children (OPerAtic) trial is to identify the best strategy to de-implement unnecessary postoperative antibiotics in children undergoing low risk (i.e., clean and clean-contaminated) surgeries as recommended by the CDC and AAP. To achieve this goal, we will (1) develop two theoretically-informed strategies for reducing postoperative antibiotic prophylaxis in pediatric surgical cases considered low-risk for an SSI, and (2) compare the two strategies using a stepped-wedge cluster randomized research design in nine US children’s hospitals to determine efficacy and potential for implementation. In order to assess the above, we will (1) evaluate the impact of the de-implementation strategies on the rate of unnecessary postoperative antibiotic prophylaxis and on key clinical outcomes (e.g., SSI, CDI); and (2) assess each strategy by evaluating key implementation processes and outcomes (e.g., penetration). Ultimately, the enhanced uptake of evidence (antibiotic guidelines) via facilitation (de-implementation strategy delivered by ASP clinicians) will improve the clinical outcomes related to antibiotic use and CDI.

## Methods

### Study setting

This study will be conducted at nine tertiary-care children’s hospitals in the US that are members of the SHaring Antimicrobial Reports for Pediatric Stewardship (SHARPS) Collaborative and the National Surgical Quality Improvement Project-Pediatrics (NSQIP-P). The SHARPS Collaborative is comprised of over 70 hospitals that care for children dedicated to improving the use of antibiotics in all healthcare settings (http://pediatrics.wustl.edu/sharps). All hospitals from the SHARPS Collaborative in this study have an active ASP with dedicated financial support for a pediatric infectious diseases physician and pharmacist. Hospitals in NSQIP-P focus on improving the overall quality of surgical care through robust data collection performed by a dedicated data abstractor. Since 2008, hospitals in NSQIP-P have collected clinical and outcomes data, including rates of SSIs and CDI. Starting in July of 2018, prophylactic antibiotic use, including post-operative antibiotic use has been collected.

### Conceptual frameworks

This study is guided by several conceptual frameworks (Fig. 1) that inform the identification and assessment of determinants [18, 19], implementation processes [19, 20], and the evaluation of implementation and clinical outcomes [21].

**Fig. 1 Fig1:**
[figure not shown]
The use of iPARIHS, ERIC, COM-B, and Implementation Outcomes Framework in the development of the study design as well as their contributions to evaluation of implementation process and outcomes [18–21]

First, the Integrated Framework for Promoting Action on Research Implementation in Health Services (i-PARIHS) framework will inform our understanding of both implementation determinants and processes to de-implementation [19, 22]. i-PARIHS has been successfully used in a number of clinical settings [19, 23, 24], and its four domains are particularly well suited to inform determinants of de-implementation (i.e., the innovation, recipients, and context) and processes that may be necessary to ensure effective de-implementation (i.e., facilitation). *Innovation* describes the evidence and knowledge regarding a particular issue, as well as the qualities of the evidence that may influence how it is perceived by the potential user, recognizing that evidence may or may not be valuable to the end user based on local circumstances and priorities. *Recipients* are actors involved in (de-)implementation who may be affected by and influence the (de-)implementation of evidence. The COM-B framework [18] will be used to assess whether antimicrobial stewards have the capability, opportunity, and motivation to change order sets. *Context* characterizes the circumstances in which knowledge and innovation uptake occurs, consisting of multiple factors at the micro, meso, and macro levels. Finally, integral to this framework is *facilitation* as the active mechanism by which (de-) implementation of evidence occurs, making it an ideal fit for the current research proposal given that we are testing facilitation as a de-implementation strategy.

For this study, implementation of new evidence is facilitated by assessing and responding to both the evidence and recipients within their contextual setting. This requires an individual acting in a facilitating role (i.e., an antibiotic steward) with strategies and actions to enable evidence uptake and implementation. The Expert Recommendations for Implementing Change (ERIC) compilation [20] will be used to guide and categorize the implementation strategies used by antimicrobial stewardship teams. These strategies informed the facilitation training that will be provided to hospital teams in order to improve use of evidence-based implementation strategies, and will also be used to inform qualitative findings that will document the types of strategies that antimicrobial stewardship teams actually employ.

Finally, the Proctor and colleagues’ [21] Implementation Outcomes Framework will inform the selection and operationalization of implementation outcomes, such as acceptability, feasibility, appropriateness, and penetration. Additionally, iPARIHS, ERIC, and the Implementation Outcomes Framework will help inform coding of monthly qualitative interviews. These interviews will be coded using deductive content analysis in their respective domains: outcomes of practice change (Implementation Outcomes Framework), the process of facilitation and strategies that the teams utilize (iPARIHS and ERIC), and barriers to practice change (iPARIHS) [19–21, 25].

### Study design

A stepped-wedged cluster-randomized trial will be conducted for 3 years (Fig. 2) [26]. We have selected this design because it (1) allows for effective implementation of the intervention at multiple sites across the study period, as synchronized implementation at a large number of sites can be difficult; (2) provides the best opportunity to thoroughly evaluate implementation and clinical outcomes since all sites will implement both interventions [27]; and (3) permits all participating hospitals to receive the ASP facilitation intervention, which will increase participation [28].

### Study interventions

#### Control intervention (order set review and modification)

For this intervention, ASP teams participate in a brief 30 min webinar providing education about current evidence related to surgical prophylaxis and simple guidance on how to eliminate excess antibiotic doses. ASP teams are encouraged to obtain the electronic order sets used in post-operative cases among surgical specialties and modify them to eliminate any post-operative antibiotics in cases determined to be clean or clean-contaminated. If an order set does not exist for a surgical procedure, ASPs are encouraged to create an order set that does not have post-operative antibiotics. This intervention was chosen as a cost-effective strategy that has been effective in improving surgical antibiotic prophylaxis but has not been rigorously tested [17, 29]. Furthermore, existing literature indicates some kind of intervention over education alone is needed to prompt improvement [30]. Thus, we opted to select a relatively minimal intervention rather than no intervention at all.

#### Experimental intervention (enhanced ASP facilitation)

The experimental intervention will involve training the ASP teams in facilitation strategies in addition to conducting order set review and modification. We hypothesize that order set modifications will be more effective paired with facilitation training by fostering better engagement between ASP teams and surgeons, such as helping negotiate different communication styles and understanding of relevant data presentation. The facilitation guide will be based on the iPARIHS framework and education on implementation strategies informed by the ERIC framework [19, 20]. The study team will serve as external facilitators to train each ASP team (internal facilitators) to provide them the necessary skill sets to enhance their ability to modify the post-operative order sets. Each site will receive training in facilitation during a two-day workshop led by experts in implementation science ([name]) and pediatric antibiotic stewardship ([name]). The workshop leaders received facilitation training through the US Department of Veterans Affairs Quality Enhancement Research Initiative (QUERI) Behavioral Health Implementation Facilitation Training Hub [31].

The workshop led at each site will begin with assessing the team’s current success at changing order sets and review of the sites relevant clinical data from NSQIP-P. The ASP teams will then receive training in the following: communication, evidence presentation, capacity assessments, team building, use of implementation strategies, quality improvement methods, and disseminating information among multi-professional teams [32–34]. Role playing will be used to build and improve skills involving communication, team building, and conflict resolution. Quality improvement methods will be discussed focusing on the importance and utility of plan, do, study, act cycles [34–36]. The workshop will end on the topic of data presentation: the principles of evidence presentation and ways of presenting data. Following this, teams will have monthly phone calls to trouble shoot and discuss implementation and facilitation strategies.

#### Data collection

Using surveys, interviews, and clinical data, we will evaluate both implementation and clinical outcomes [21, 37]. In general, implementation outcomes will indicate the ease with which the proposed strategies can be implemented in a variety of contexts in the future. In combination with clinical outcomes (e.g., rates of unnecessary antibiotic use), we will test whether order set review and modification plus enhanced ASP facilitation provides additional benefit over the standard order set review and modification strategy.

### Baseline data

Prior to the start of the control intervention, hospital demographic information (e.g., bed size, surgical volumes, etc.) and the characteristics of the hospital’s ASP program (e.g., strategies utilized, locations where strategies implemented, and metrics utilized) will be collected. Additionally, this survey, will obtain specific information on efforts by the ASP at each site toward eliminating post-operative antibiotic use in the surgical subspecialties.

### Clinical data

Three-months following each step, clinical data for the 6 months of the step will be obtained from NSQIP-P. These data will include post-operative antibiotic use, surgical site infection, and *Clostridioides difficile* infection. This 3-month delay allows time for data collection and monitoring for complications including SSIs and CDIs. These measures are the same in both the control and intervention phase of the trial.

At each hospital, data collection will occur for 35 cases every 8 days, thereby providing clinical and outcome data for up to 1500 cases per year. Hospitals will preferentially sample up to 4 cases of the following high-volume cases: appendectomies, ventriculoperitoneal shunt placements, spinal fusions, ureteral re-implantation, and tracheostomy placement in children less than 2 years of age. Given current estimates of case volume and case mix, the “typical” participating hospital will collect about 8-12 of these up-sampled cases. The remaining cases will be randomly sampled across the 640 CPT codes until a total of 35 cases are included for those 8 days. While this sampling will not collect all cases, studies of appendectomy cases showed that NSQIP-P data were representative of the entire institutional experience [38].

Surgical procedures collected by NSQIP-P data abstractor at the hospitals participating are eligible for inclusion if they have a wound class of clean or clean-contaminated. Children undergoing surgeries due to infection will be excluded.

Data elements collected for each surgical case include demographics (e.g., age, sex, date of procedure), type of procedure, wound class (clean, clean-contaminated, contaminated, or dirty), co-morbidities, and resources utilized for the surgical case. Antibiotic prophylaxis data collected will include type of antibiotic, appropriate perioperative timing (i.e., within one hour prior to incision), whether redosing occurred, and duration of postoperative antibiotic prophylaxis.

The primary clinical outcome will be the percentage of clean and clean-contaminated cases that receive unnecessary post-operative antibiotics. Secondary clinical outcomes will include the rate of SSIs and CDIs.

### Implementation data

Process: Semi-structured interviews (see Supplemental file A for interview guide) will be conducted with a member of the ASP team at each site monthly through the duration of the trial. These interviews will be conducted virtually via zoom and will last ~30 min. We will assess the progress of the site in identifying, reviewing, and changing current surgical order sets and implementing new order sets that do not contain post-operative orders for antibiotics. Furthermore, information will be obtained regarding current barriers, and additional work being done to eliminate unnecessary post-operative antibiotics (e.g., stakeholder meetings).Outcomes:
*Acceptability, Appropriateness, Feasibility*: We will assess the acceptability, appropriateness, and feasibility of each strategy using psychometrically strong and pragmatic survey measures [39], which will be distributed once during each step. All members of the ASP team will complete these surveys regarding the intervention(s) currently being implemented by the ASP. Therefore, during control, participants will complete the surveys for acceptability, appropriateness, and feasibility in relation to changing order sets as an implementation strategy. During the intervention, participants will complete separate surveys to independently evaluate changing order sets and the use of facilitation techniques.*Penetration* will be measured as the number of order sets modified or newly created. These data will be collected monthly through the web-based semi-structured interview.*Health beliefs*: Once per step, each member of the antibiotic stewardship team will be asked three health belief questions modeled off the COM-B system [18]. These questions assess the participants’ belief in their capability, motivation, and opportunity to change post-operative order sets.

## Statistical analysis plan

### Clinical outcomes

#### Primary hypothesis

Our primary hypothesis is that the experimental intervention of enhanced ASP facilitation will decrease the percentage of cases receiving unnecessary postoperative antibiotic prophylaxis from baseline more than the control intervention. To test this hypothesis, statistical model (1) will be used. With each cross-section consisting of *m* patients, we assume a model in which the logit of outcome for patient *i* at times *t* = 0, ⋯, *T* in hospital *k* = 1, ⋯, *K*, and cluster *l* = 1, 2, 3 is
1$$ \mathrm{logit}\left({\pi}_{itkl}\right)=\gamma +{\theta}_t+{A}_{lt}\delta +{x}_{kl}+{h}_{tkl}+{\varepsilon}_{itkl}, $$

where *π*_*itkl*_ is probability of percentage of unnecessary postoperative antibiotic prophylaxis, $$ {\varepsilon}_{itkl}\sim N\left(0,{\sigma}_{\mathrm{error}}^2\right) $$, $$ {h}_{tkl}\sim N\left(0,{\sigma}_{\mathrm{time}\mid \mathrm{clinic}}^2\right) $$, $$ {x}_{kl}\sim N\left(0,{\sigma}_{\mathrm{clinic}}^2\right) $$, with *ε*_*itkl*_, *h*_*tkl*_, and *x*_*kl*_ are all independent of one another, and
$$ {A}_{lt}=\left\{\begin{array}{c}1\ \mathrm{if}\ \mathrm{cluster}\ l\ i\mathrm{s}\ \mathrm{receiving}\ \mathrm{the}\ \mathrm{intervention}\ \mathrm{at}\ \mathrm{time}\ t\\ {}0\ \mathrm{if}\ \mathrm{cluster}\ l\ i\mathrm{s}\ \mathrm{receiving}\ \mathrm{the}\ \mathrm{control}\ \mathrm{at}\ \mathrm{time}\ t\kern2.5em \end{array}\right. $$

This hierarchical, multilevel model includes a fixed effect of time *θ*_*t*_, we set *θ*_0_ = 0. The parameter *δ* is the treatment effect; we assume that the treatment effect is maintained once the intervention has been initiated. The fixed effect *θ*_*t*_ must be estimated independently of the treatment effect so that a systematic change over time is not mistaken for an effect of treatment. The model also includes random effect, variation between clusters (*x*_*kl*_), and variation between times within a hospital (*h*_*tkl*_).

Unadjusted analysis through model (1) will be conducted, and an adjusted model will be developed. The following data elements will potentially be included in this model: hospital, age, surgical subspecialty (e.g., orthopedics, ENT, etc.), type of procedure, duration of hospitalization, and co-morbidities. The estimated intervention effect will be reported as odds ratio with 95% CIs and *p* values. The tests will be two-sided and the significance level will be set at 0.05. The statistical package SAS 9.4 will be used for all statistical calculations.

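### Duration of hospitalization, known only after surgery, is a candidate covariate in the adjusted model of the primary outcome; if included, the adjusted odds ratio may not estimate the total effect of facilitation

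*Protocol article*

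**What the plan says.** All of this is in the protocol article.

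- **Primary test.** Under Primary hypothesis: "To test this hypothesis, statistical model (1) will be used". Model (1) contains a period effect, the treatment indicator, a hospital random effect and a hospital-by-time random effect. It has no patient-level covariates.
- **Two analyses.** The same section continues: "Unadjusted analysis through model (1) will be conducted, and an adjusted model will be developed".
- **Candidate covariates.** The list for the adjusted model reads "hospital, age, surgical subspecialty (e.g., orthopedics, ENT, etc.), type of procedure, duration of hospitalization, and co-morbidities". Its status is left open by the words that introduce it: "The following data elements will potentially be included in this model". Nothing limits the duration to the stay before surgery, and no reason is given for conditioning on it.
- **Reporting.** On the effect measure, the section states "The estimated intervention effect will be reported as odds ratio with 95% CIs and", and the sentence ends by naming the test result as well. On testing, it states "The tests will be two-sided and the significance level will be set at 0.05". The text does not say whether the unadjusted or the adjusted odds ratio leads the report.
- **Outcome.** Under Clinical data: "The primary clinical outcome will be the percentage of clean and clean-contaminated cases that receive unnecessary post-operative antibiotics".
- **Intervention.** Under Experimental intervention, training is meant to give stewardship teams the skills to "enhance their ability to modify the post-operative order sets".

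**The concern.** Age, subspecialty, type of procedure and co-morbidities are settled before or at surgery, so facilitation cannot change them for a given case. Duration of hospitalization is different. It is known only at discharge, after the post-operative order set has been used and the antibiotic given or withheld. It can be related to the analysis in three ways:

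- facilitation may alter it through changes in post-operative practice other than the antibiotic;
- the antibiotic itself may alter it;
- it may share unmeasured severity with antibiotic use, so that conditioning on it links treatment period and severity if facilitation also affects stay.

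In the first and third cases the treatment coefficient, given stay, need not equal the total effect δ of model (1). The adjusted odds ratio could then differ from the unadjusted one for a reason unrelated to case mix, and a reader would probably take the difference for control of confounding. With nine hospitals, an adjustment for case mix may carry real weight in interpretation, so it should be clean.

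**Working it through.** **1. The plan's own figure.** Power estimates gives 46 cases per step per hospital, 9 hospitals, 33% against 13%, ICC 0.121, cluster auto-correlation 0.328, significance level 0.05 and 80% power. Six-month steps over three years give 6 periods.

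- Averaged binomial variance: (0.33×0.67 + 0.13×0.87)/2 = (0.2211 + 0.1131)/2 = 0.1671.
- Variance of a hospital-period mean: 0.1671 × [(1−0.121)/46 + 0.121] = 0.0234. Covariance between periods in one hospital: 0.1671 × 0.121 × 0.328 = 0.0066.
- Generalised least squares with period effects, 3 sequences of 3 hospitals: SE = 0.0713. Power = Φ(0.20/0.0713 − 1.96) = 0.800. The smallest number per hospital-step that reaches 80% is 46.

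The stated figure reproduces. No covariate enters it, so changing the covariate list leaves it as it is.

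**2. What conditioning on stay does.** The documents give no length-of-stay figures, so everything here is assumption and serves only to show the sign. Let Y be the antibiotic outcome and A the facilitation indicator. Let log stay be normal with mean μ + λY + γA and variance σ². By Bayes' rule,

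logit P(Y=1 | A, stay) = logit P(Y=1 | A) + λ(log stay − μ − γA)/σ² − λ²/(2σ²).

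The treatment coefficient given stay is therefore δ − λγ/σ².

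From the planning rates, the odds ratio is (0.13/0.87)/(0.33/0.67) = 0.303, so δ = −1.193. Taking σ² = 0.6² + 0.4² = 0.52:

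| Assumption | λ | γ | −λγ/σ² | OR without stay | OR with stay |
|---|---|---|---|---|---|
| Stay responds only to the antibiotic | 0.3 or 0.6 | 0 | 0 | 0.303 | 0.303 |
| Facilitation also shortens stay | 0.3 | −0.15 | +0.087 | 0.303 | exp(−1.106) = 0.331 |
| The same, stronger | 0.6 | −0.30 | +0.346 | 0.303 | exp(−0.847) = 0.429 |
| Facilitation lengthens stay | 0.3 | +0.15 | −0.087 | 0.303 | exp(−1.279) = 0.278 |

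A simulation with 9 hospitals, 6 periods and hospital and period effects gave the same pattern. Without and with stay, the odds ratios were:

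- 0.302 and 0.302 (λ = 0.3) or 0.304 and 0.301 (λ = 0.6) when stay responds only to the antibiotic;
- 0.306 and 0.333 (λ = 0.3, γ = −0.15);
- 0.301 and 0.424 (λ = 0.6, γ = −0.30);
- 0.301 and 0.276 (λ = 0.3, γ = +0.15).

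**3. Shared severity.** When unmeasured severity raised both antibiotic use and stay, the simulated odds ratio moved from 0.347 to 0.375 if facilitation also shortened stay (γ = −0.2, λ = 0). It moved from 0.352 to 0.327 if the antibiotic lengthened stay (λ = 0.3, γ = 0). Some movement in this setting is only the non-collapsibility of the odds ratio: with λ = γ = 0 it still moved from 0.350 to 0.339.

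**4. Reading.** The sign depends on λ and γ, and the documents give neither.

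**The case against.** The case for leaving the list alone has several parts.

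- **The primary test does not use the list.** Model (1) is named for the primary hypothesis and has no patient covariates. This stands, and it limits the point to the adjusted estimate.
- **Inclusion is only potential, and the final choice may be left to a full analysis plan.** It is true that inclusion is not certain. But the article names this variable as a candidate. That is a stated choice, not missing detail, and it can be corrected where it stands.
- **Fewer doses leading to earlier discharge does no harm by itself.** This is right. On that path stay responds only to the outcome, and the odds ratio stays at 0.303. A reader might infer that this path alone dilutes the effect, but it does not. Bias needs a separate effect of facilitation on stay, or shared severity. The documents describe no separate route, but they do not exclude one: the training covers communication and engagement with surgeons as well as the order sets.
- **A route through surgical site infection is weak.** This stands: the article expects no difference in infection rates and calls such infections infrequent.

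A reader might also infer that adjustment must shrink the effect by some definite fraction. No such figure can be supported, because it would rest on an assumed effect of facilitation on stay.

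Finally, a reader might infer that listing hospital is an error because model (1) already has a hospital random effect. That is not supported either. The word may simply name that term, and a fixed hospital effect with nine hospitals is an accepted choice that still estimates treatment within hospitals over time.

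**Conclusion.** The point holds in a limited form. Duration of hospitalization is a poor candidate for the adjusted model, because it is known only after the intervention and the outcome have acted. If it is included, the adjusted odds ratio may not estimate the total effect of facilitation.

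The documents do not determine the size or direction of the bias. With no shared severity and antibiotics associated with longer stay, it is nil when stay responds only to the antibiotic, towards 1 when facilitation separately shortens stay, and away from 1 when facilitation lengthens it. Shared severity can add movement either way. The figures in the working show signs under assumed values and are not estimates for this trial. The unadjusted primary test through model (1) and the sample size are unaffected.

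**What to change.** Delete duration of hospitalization from the candidate list. State that adjustment is restricted to variables fixed before or at surgery: age, surgical subspecialty, type of procedure and co-morbidities, added to model (1) with its hospital term kept. If a model containing stay is of interest, present it as a labelled sensitivity analysis and say that its odds ratio is conditional on a variable measured after the intervention.

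The cost is about one line of text. The Clinical data section already lists age, type of procedure and co-morbidities among the collected elements, and subspecialty is already on the article's own candidate list. The number of cases and the power are unchanged.
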